#### Exclusions

Patients with cognitive impairment (MMSE <24) are excluded from the study given the paucity of data on the use of fear of falling measures in this patient group and the difficulties in conducting CBTIs in those with significant cognitive impairment. Patients with a life expectancy of <1 year and those requiring psychosocial interventions unrelated to fear of falling will also be excluded.

### Ethical and regulatory arrangements

Favourable ethical opinion from the Newcastle and North Tyneside 1 Research Ethics Committee (Phase 1 REC reference: 11/NE/0090 Phase 2 REC Reference: 12/NE/0006) has been obtained and subsequent Research and Development and Caldicott approvals have been granted to all parts of the study. The Newcastle upon Tyne Hospitals NHS Foundation Trust is the sponsor for the trial.

### Risks and anticipated benefits for trial participants and society

The potential risks associated with the STRIDE study are few. The main anticipated issue centres on the potential for patients to gain confidence and lose their fear of falling in a way that is inconsistent with their improvement (or lack thereof) in physical function. In other words, patients who have hitherto considerably limited activity through fear of falling have the potential to increase activity levels through amelioration of the condition with the CBTI before any physical interventions have been able to take effect and therefore to increase their risk of an actual fall. In practice, this is unlikely given the prolonged course of the CBTI. We believe the potential benefits to individuals and society in terms of increasing activity, avoidance of social isolation, enhancement of independence and avoidance of injuries and hospitalisations from examining the effectiveness of psychological interventions in people with fear of falling are, nevertheless, worth such risks.

### Sample size

#### Phase 1

Anxiety disorder tends to have a fairly narrow range of maintaining factors which, most usually, are catastrophic beliefs and activity avoidance. The psychological constructs of fear of falling suggest that a similar range of maintaining factors is likely to be in operation. We therefore expected the number of patients needed to consistently identify such factors to be relatively small; prior work from our group showed that saturation was reached with 12 [23], and will be no more than 30, interviews. Phase I was successfully completed with 15 such interviews.

#### Phase 2

Primary outcome is change in fear of falling (as measured by the FES-I) at 12 months. The estimated standard deviation is 12.5 [20]; the difference in group means that we wish to be able to detect is 4.0 (per clinical judgment in combination with observed effects in a range of studies) [18,35] corresponding to a standardized effect size of 0.32. Accordingly, the number required to provide full outcome data (80% power, 5% significance level) is 154 per group, or 308 in total. To allow for 25% drop-out (from previous experience in falls studies run locally with this patient group and from the CBT in fear of falling literature), we will recruit 412 subjects.

### Qualitative process evaluation (running across Phases 1 and 2)

Participants in the process evaluation will include members of the trial team (n = 10-15, each interviewed two to three times during the project), professionals involved in the delivery of the intervention (n = 5-7, interviewed at multiple points during the study) and patients who would be eligible for the CBTI (Phase 1 n = 10) and those receiving the intervention (Phase 2 n = 20).

### Statistical analysis

The primary analysis will be based on fear of falling (FES-I) assessed at baseline and 12 months. The change in fear of falling will be analysed using analysis of covariance. The dependent variable will be the FES-I score at 12 months; baseline FES-I will be included as a covariate. Stratification variables (gender, referral to strength and balance training classes) will be included as fixed effects. Potential differences between therapists will be investigated by fitting an additional random effect. Secondary outcomes will be assessed using similar methods.

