While such physical interventions may be of benefit in selected populations, the profile of the disorder and its psychosocial complications suggest that well-designed psychological interventions may help ameliorate fear of falling more definitively. Several studies have examined an explicitly cognitive behavioural therapeutic (CBT) approach in fear of falling in community-dwelling elders, or used CBT techniques as part of a wider intervention strategy. Tennstedt *et al*.’s Matter of Balance study assessed the ability of an eight-session, 4-week group CBT with exercise instruction to improve fear of falling and related activity restriction [17]. Significant differences between intervention and control groups were seen in fear of falling as measured by the Falls Efficacy Scale (FES) [12] and activity during follow-up. The magnitude of improvement in FES scores attenuated over time, prompting the authors to suggest a booster session should be used in future studies and in clinical practice [17]. Clemson *et al.* similarly used what they described as a ‘small-group learning environment’ (though in practice, some of the methods used included CBTs) of 12 individuals per group for 2 hours per session over 7 weeks to improve self-efficacy and reduce falls [18]. The intervention incorporated a variety of learning strategies to facilitate behaviour change, including education regarding exercises to improve falls risks, medication and home environmental review and medication management [18]. There was a 31% reduction in falls (relative risk 0.69, 95% CI 0.50 to 0.96, *P* = 0.025) in the intervention group, though interestingly there was no corresponding change in FES scores [18]. More recently, Zijlstra and colleagues conducted a RCT of a multicomponent cognitive behavioural group intervention in older community-dwelling elders [19]. Five hundred and forty participants were drawn from a random sample of 7,431 individuals who reported (through self-report questionnaires) ‘at least some fear of falling’, though the precise method of assessment was not specified. Following randomisation, the intervention group underwent a structured 2-hour group CBT intervention based on the investigators’ previous work once weekly for 8 weeks, with booster sessions 6 months following the last session. A primary outcome was not specified, and while a power calculation was supplied based on a ‘difference of 2.5 points’, the authors fail to specify on which scale. The beginning of the trial predates widespread use of the FES-International version (FES-I) [20] (later advocated by the same group as the most appropriate measure for such studies [7]), instead using a single item question on fear of falling as well as an unspecified scale, likely to be the original FES from the description and reference supplied [19]. Other outcomes included perceived control over falling and daily activity as well as falls. There were no measures of physical function despite the prior evidence base suggesting improvement in fear of falling with the exercise-related measures as described above. All outcomes showed significant differences between control and intervention groups at 2 and 8 months follow-up, with between-group differences persisting at 14 months in fear of falling and perceived control over falling but not in the other outcome measures. There was a 30% attrition rate in the intervention group and 19.6% attrition rate in the control group [19]. The study intervention was carefully developed and grounded in CBT, but interpretation and application is hampered considerably by the lack of clarity on sample size calculation and outcome measures and the absence of generic quality-of-life measures and measures of physical functioning. Importantly, there is also no health economic analysis [19] to guide commissioners and providers of healthcare, crucial in this context because of the size of the clinical problem.

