### Effect of missing data

This is a comparatively frail population and we can expect some drop-out during the study. It is likely that those participants who are lost to follow-up during the trial may also be people with a tendency to experience poorer quality of life (in terms of fear of falling) than those who remain in the study. In this situation, the data cannot be considered to be missing at random. On the contrary, the event of a patient failing to complete the study may be informative. It is necessary to take into account any difference in drop-out rates and the non-randomness of the drop-out when comparing fear of falling per the FES-I between the two treatment groups. This will be done by jointly modelling ‘survival in the study’ and the repeated measures of fear of falling simultaneously [36] using software that has been developed as part of an MRC-funded programme of work (Grant G0400615; Statistical methodology for longitudinal studies in clinical research; Williamson PR, Diggle PJ and Henderson R). Time to drop-out will be analysed using a Cox proportion hazards model incorporating random effects. Fear of falling will be modelled using mixed models appropriate for repeated measures. A key feature of each of these models is that within each of them it is possible to fit a latent variable that can be conceptualised as the patient’s propensity to experience poor outcomes (both their likelihood to drop out of the study and their likelihood to have poorer FES-I scores). It is the inclusion of this latent variable that allows us to adjust our estimates of the treatment effect to allow for the different rates of drop-out in each group. Both models are estimated simultaneously; parameter estimates are based on maximising the joint likelihood over both the survival and repeated measures data.

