
### Outcome data collection

Primary and secondary outcomes will be measured at baseline (pre-randomisation), at 8 weeks (that is at the end of CBTI) and 6 and 12 months post-randomisation. Assessment will also be made of harms, level of social care and dependency. Weekly symptom diaries (validated in similar populations [39,68]), completed and submitted weekly for 12 months, will record falls and injuries as described previously. Data will be collected for the purpose of the process evaluation on an ongoing basis over the course of the project.

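### The primary ANCOVA uses only baseline and 12-month FES-I although the protocol calls drop-out informative, and the joint model meant to deal with this has no stated status

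*Protocol article*

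**What the plan says.** Under Sample size, the endpoint is fixed at one time point: "Primary outcome is change in fear of falling (as measured by the FES-I) at 12 months". The same section counts only patients with complete outcomes: "the number required to provide full outcome data (80% power, 5% significance level) is 154 per group, or 308 in total". It then raises recruitment to 412 to allow for 25% drop-out.

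Under Statistical analysis: "The primary analysis will be based on fear of falling (FES-I) assessed at baseline and 12 months". The model is an ANCOVA: "The dependent variable will be the FES-I score at 12 months; baseline FES-I will be included as a covariate". Gender and referral to strength and balance classes enter as fixed effects. Nothing is said there about patients who have no 12-month score, and the joint model is not mentioned.

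Under Effect of missing data, the authors expect patients who leave to be those with worse fear of falling, and conclude: "In this situation, the data cannot be considered to be missing at random". They go on: "It is necessary to take into account any difference in drop-out rates and the non-randomness of the drop-out" when FES-I is compared between the groups. The stated method is a joint model of time to drop-out and repeated FES-I, which gives its own adjusted treatment effect. The section does not call that model primary, secondary or sensitivity.

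Under Outcome data collection, outcomes are measured at baseline and "at 8 weeks (that is at the end of CBTI) and 6 and 12 months post-randomisation", so two intermediate FES-I scores are planned for every patient still in follow-up.

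**The concern.** The two analysis sections address the same comparison on the same outcome. The analysis labelled primary is sound for all randomised patients only if, given arm and the baseline covariates, drop-out carries no further information about the 12-month score. The missing-data section says the authors do not believe this. It calls an adjustment necessary and assigns it to a different model, which the primary analysis section does not mention.

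Two things are at stake. First, if more patients who are doing badly leave one arm than the other, the remaining patients are no longer comparable and the primary estimate shifts. The 8-week and 6-month scores are the best available evidence on patients who leave later, and the primary analysis does not use them. Second, the trial will hold two estimates of one effect with no prespecified reading if they disagree. That leaves room to choose the emphasis after both are known.

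**Working it through.** **1. The plan's own figures.** Inputs from Sample size: SD 12.5, difference 4.0, 80% power, 5% level (taken as two-sided), 25% drop-out.

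- Per group: 2 × (12.5 × (1.960 + 0.842) / 4.0)² = 153.3, rounded up to 154; total 308.
- Inflated by arm: 154 / 0.75 = 205.3, rounded up to 206; total 412.
- Expected without a 12-month score: 412 × 0.25 = 103. Expected completers: 412 × 0.75 = 309.

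The sample size reproduces. It also fits the plain reading of the ANCOVA, since power is counted on completers.

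**2. Completer bias by formula.** Let d₁ and d₀ be the drop-out proportions (intervention, control), and let D be the amount by which drop-outs' 12-month FES-I exceeds that of completers, taken as equal in both arms. The completer comparison then overstates benefit by (d₁ − d₀) × D. The documents give no D, so it is an assumed range. For the rates I use the earlier group CBT trial described in Background: "There was a 30% attrition rate in the intervention group and 19.6% attrition rate in the control group". So d₁ − d₀ = 0.300 − 0.196 = 0.104.

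| Assumed D (points) | Bias (points) | Share of 4.0 |
|---|---|---|
| 2 | 0.21 | 5% |
| 4 | 0.42 | 10% |
| 8 | 0.83 | 21% |
| 12.5 | 1.30 | 33% |

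With 25% in both arms and the same D, the bias is 0. With 25% in both arms but D differing by 4 or 8 points, it is 0.25 × 4 = 1.0 or 0.25 × 8 = 2.0 points.

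For scale, completers would number 206 × 0.70 = 144 and 206 × 0.804 = 166. The unadjusted standard error is 12.5 × √(1/144.2 + 1/165.6) = 1.42. A nominal two-sided 5% error becomes about 5.9% at a bias of 0.4, 8.7% at 0.8 and 15.0% at 1.3.

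**3. Simulation with repeated scores.** Assumptions: 2,000 trials per scenario, 206 per arm, SD 12.5, true effect 4.0, visit correlations 0.5 to 0.7, all drop-out after 6 months. Drop-out follows a logistic model calibrated to the stated rates. Strength is the log-odds per SD of FES-I. The comparator predicts missing 12-month scores from baseline, 8-week and 6-month scores within arm, which is equivalent to a likelihood-based repeated-measures analysis when only the last visit is missing. Ranges reflect repeated simulation runs.

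| Drop-out depends on | Strength (int. / control) | Rates | Completer ANCOVA | Using interim scores |
|---|---|---|---|---|
| 6-month score | 1.0 / 1.0 | 30% / 19.6% | 4.41–4.46 | 3.95–4.04 |
| 6-month score | 1.0 / 0.5 | 30% / 19.6% | 4.88–4.89 | 3.95–4.04 |
| 6-month score | 1.0 / 1.0 | 25% / 25% | about 4.0 | about 4.0 |
| 12-month score, unobserved | 1.0 / 1.0 | 30% / 19.6% | 4.81 | 4.54–4.56 |

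In the first two rows the ANCOVA bias is 0.41 to 0.89 points, or 10% to 22% of 4.0, in favour of the intervention. With a true effect of zero, the completer ANCOVA's two-sided false-positive rate in those rows was about 7% and 11%. Using the interim scores also gives a slightly smaller standard error.

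A stress case with opposite-sign dependence (−0.7 / 0.7) gives 2.22 to 2.33 and power of 45% to 48%. It is treated below.

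**The case against.** **The ranking is already there.** Only the ANCOVA is called primary, and the joint model sits under a separate missing-data heading. This stands. A reader might infer that the plan has two competing primary analyses, and the text does not support that. What remains is that the missing-data section presents the joint model as the way the group comparison will be adjusted, without giving it a status or a rule for disagreement. A condensed article may leave such detail to a fuller document. But the tension between the stated assumption and the chosen primary model is in the article itself.

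**The early visits are not ignored.** The joint model includes a repeated-measures part, so the charge applies to the ANCOVA only. Nor does the article literally say complete cases only. That is the plain reading of a two-time-point ANCOVA with no stated handling of missing scores, supported by the sample size wording.

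**The proposed replacement also assumes missing at random.** This is the strongest objection, and it stands in part. The simulation rows on the 6-month score favour the repeated-measures model by construction, because drop-out there depends only on observed scores. When drop-out follows the unobserved 12-month score, most of the bias remains (4.54 to 4.56, against 4.81 for the ANCOVA). The joint model itself was not simulated, so nothing here shows it to be worse. The repeated-measures model rests on a weaker assumption than the ANCOVA, but it does not answer the authors' worry alone.

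**The harm depends on arm differences.** With equal rates and equal dependence the bias is essentially nil. A reader might take the stress case, an effect nearly halved, as the likely damage. The protocol expects drop-outs to do worse and mentions no reversal between arms, so that case should not be used as the size of the problem.

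**Conclusion.** The concern holds in a limited form. The primary ANCOVA, plainly read, omits about a quarter of randomised patients and their intermediate scores, under an assumption that the next section rejects. The joint model that is meant to repair this has no declared role and no rule for discordance.

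The likely size is modest: about 0.4 to 0.9 FES-I points on a 4.0-point target for same-direction dependence on the 6-month score, and essentially nil if rates and dependence are equal in both arms. These figures rest on assumed visit correlations and drop-out strengths, and on attrition borrowed from an earlier group-based trial that may not apply to individual therapy.

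A reader might go further and infer that the primary result will be seriously wrong or that the sample size is mistaken. The documents support neither: the sample size reproduces, and they give no figure for how drop-outs differ from completers. This is a should-fix point rather than a must-fix one.

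**What to change.** Before outcome data are seen by arm, make the primary analysis a likelihood-based repeated-measures model on FES-I at 8 weeks, 6 months and 12 months. Include baseline FES-I, the stratification factors, arm, visit and arm-by-visit, with an unstructured covariance. The 12-month contrast is the primary estimate, and every randomised patient with any follow-up score contributes.

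Name two prespecified sensitivity analyses for non-random drop-out: the joint model already described, and a delta-adjusted analysis in which the shift for missing scores is varied separately by arm. State how discordant results will be read. For example, the repeated-measures estimate decides, the joint-model estimate is reported beside it, and the conclusion is qualified if a plausible delta overturns it.

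The cost is wording and some programming, with no new data, visits or patients. The downside is that the primary model still assumes missing at random given observed scores. It cannot fully remove bias from drop-out driven by unobserved scores, so the joint model must be kept and reported alongside it.

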**Figure 1 F1:**
[figure not shown]
Consort flow diagram illustrating the STRIDE study.

### Phase 1

Pilot study developing a cognitive behavioural model tailored to older patients [27] with fear of falling, based on the Medical Research Council (MRC) model of complex intervention development [28] and incorporating elements of previously successful CBT-based interventions [16-19]. Patients with significant fear of falling attending our community falls service were included in this phase of the study, and HCAs trained to deliver the intervention.

### Phase 2

Parallel-group patient RCT of the novel CBTI plus usual multidisciplinary care versus usual multidisciplinary care alone in patients with significant fear of falling attending multidisciplinary falls services. Patients are randomised in a 1:1 ratio, using a web-based system to ensure concealment of allocation, to intervention and control groups. Randomisation is stratified by gender (to avoid any potential sex differences in the response of older individuals to CBT-type interventions) and by whether the patient has been referred for strength and balance training. Study centre (random effect) and pain score (fixed effect) are also entered in to the randomisation system as stratification variables. Fear of falling is well documented in fallers from 40 years to extreme old age [6-10]; accordingly, we do not feel that stratification by age will add to the assessment of the intervention’s effectiveness; in addition, we can find no compelling evidence that older individuals respond to CBT differently. Our study is an individually randomised trial, delivered by three therapists (HCAs), and as such groups could theoretically be open to contamination (that is patients allocated to the control condition receiving CBTI). We believe that this risk is minimal, particularly at clinician level as the HCAs delivering the CBTI during Phase 2 will only be seeing the intervention group of patients and will not be part of the teams delivering usual care.

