#### Phase 2: RCT of CBTI versus usual care

Patients are recruited in the falls clinics following appropriate identification of inclusion and exclusion criteria. They are then given study literature and an expression of interest form for return by post. A recruitment visit is then arranged, and informed written consent obtained. Patients are randomised in 1:1 ratio, with stratification by gender and referral to strength and balance training classes to CBTI plus treatment as usual, or control (treatment as usual) groups. CBTI sessions last approximately 45 minutes with 15 minutes of preparation time, and are based on an individualised formulation that identifies and targets the factors maintaining fear of falling for that individual. Treatment is weekly for 8 weeks, with a single reinforcement CBTI session 6 months after the last CBTI session. Follow-up will be for 12 months to assess the longevity of CBTI’s effects. Treatment as usual comprises the routine care that all patients at the falls clinic receive. All undergo detailed falls-oriented physiotherapy assessment, lying and standing blood pressure measurement, electrocardiography, bone health assessment using the FRAX™ [31] tool, Mini-Mental State Examination (MMSE) [32], 15-item Geriatric Depression Scale [33], FES-I [19] and visual acuity assessment [1]. A comprehensive overview with a falls expert, utilising the information gained from the other parts of the evaluation, rounds off the assessment.

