## Discussion and trial status

Phase I of the study was completed successfully, with the development of training materials and successful recruitment and training of the HCAs in delivering the CBTI to time and target. Despite pre-study qualitative work suggesting an appropriate timetable for recruitment, Phase II began to run into recruitment problems from an early stage. A recovery plan was put in place following qualitative interviews with potential study participants, actual participants, carers and staff members to identify barriers and promoters of recruitment. With the assistance of the TSC and agreement with the DMEC and the funder, NIHR HTA, alongside appropriate permissions and approvals, two further sites to the original single study site were brought on board. A 7-month extension to the study was granted, with the desired outcome of the appropriate recruitment target within reach at time of writing.

The CBTI has uncovered interesting insights into fear of falling that will be of use to researchers trying to improve this nebulous and limiting condition regardless of the outcome of the RCT. The use of non-mental health practitioners in this role has been studied previously with our experience in this study reinforcing the potential for suitably trained and supervised HCA assistant grade staff to perform such therapies. This has clear implications for cash-strapped health providers with a relatively small base of clinical psychologists and therapists available to manage such ubiquitous clinical problems. Similarly, the process evaluation has already yielded important observations that will be of use to researchers and those implementing healthcare innovations.

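### The primary ANCOVA adjusts for two of the four randomisation stratification variables; study centre and pain score are left out, which makes the analysis conservative if they are prognostic

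*Protocol article*

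**What the plan says.** The protocol article describes the stratification in three places.

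- **Methods, Phase 2 (after Figure 1).** Gender comes first: "Randomisation is stratified by gender (to avoid any potential sex differences in the response of older individuals to CBT-type interventions". Referral for strength and balance training follows as the second factor. Two more are then added: "Study centre (random effect) and pain score (fixed effect) are also entered in to the randomisation system as stratification variables". That makes four.
- **Phase 2: RCT of CBTI versus usual care.** Only two are given: "Patients are randomised in 1:1 ratio, with stratification by gender and referral to strength and balance training classes".
- **Statistical analysis.** The primary model is an analysis of covariance: "The dependent variable will be the FES-I score at 12 months; baseline FES-I will be included as a covariate". For the strata: "Stratification variables (gender, referral to strength and balance training classes) will be included as fixed effects". The only random effect mentioned is for therapist: "Potential differences between therapists will be investigated by fitting an additional random effect". Secondary outcomes are to be handled by similar methods.

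The Discussion and trial status section gives the number of centres: "two further sites to the original single study site were brought on board", so three in all.

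**The concern.** The Statistical analysis section is not silent on this point. It adopts the principle that stratification variables go into the model, and then gives a closed list that omits two of the four named under Phase 2. By its own principle, centre and pain score belong in the primary model.

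Stratified allocation makes the arms alike on centre and pain score, which lowers the true sampling variance of the treatment difference if those variables are prognostic. A model without them leaves their contribution in the residual, so the reported standard error does not reflect the gain. The interval is then wider, and the test less likely to reject, than the design warrants. The secondary outcomes inherit the same model.

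**Working it through.** **Inputs from the Sample size section:** difference 4.0, SD 12.5 (standardised 0.32), 80% power, 5% significance (two-sided assumed), 154 per group, 308 in total, 25% drop-out, 412 recruited.

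**Input not in the document:** R², the share of residual variance in 12-month FES-I that centre and pain score explain after the other model terms. The range 0 to 0.15 is an assumption.

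**Step 1: reproduce the stated sample size.** n per arm = 2(1.96 + 0.8416)²/0.32² = 153.3, rounded up to 154. With drop-out, 154/0.75 = 205.3, so 206 per arm and 412 in total. The stated figures reproduce, and nothing below changes them.

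**Step 2: standard errors.** The model without the two strata reports SE = 12.5 × √(2/154) = 1.4245. With the arms balanced on these strata, the true SE is 1.4245 × √(1 − R²), which is also what the fully adjusted model reports.

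**Step 3: consequences** (normal approximation).

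- Interval width, omitted relative to adjusted: 1/√(1 − R²).
- Actual type I error when omitted: 2[1 − Φ(1.96/√(1 − R²))].
- Power, adjusted: Φ(4/(1.4245√(1 − R²)) − 1.96).
- Power, omitted: Φ((4 − 1.96 × 1.4245)/(1.4245√(1 − R²))).

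| R² | CI too wide by | Actual type I error | Power, adjusted | Power, omitted | Difference (points) |
|---|---|---|---|---|---|
| 0 | 0% | 5.0% | 80.2% | 80.2% | 0 |
| 0.02 | 1.0% | 4.8% | 81.0% | 80.4% | 0.5 |
| 0.05 | 2.6% | 4.4% | 82.1% | 80.8% | 1.4 |
| 0.10 | 5.4% | 3.9% | 84.1% | 81.4% | 2.7 |
| 0.15 | 8.5% | 3.4% | 86.1% | 82.1% | 4.0 |

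Differences are taken before rounding.

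**Step 4: allow for the baseline FES-I covariate.** The Sample size section uses the unadjusted SD, but the planned model already includes baseline FES-I. The document gives no baseline-to-12-month correlation, so 0.5 and 0.7 are assumed. The residual SD becomes 12.5√(1 − ρ²).

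- ρ = 0.5: power is about 90% before centre and pain are considered. The difference is 0.8 points at R² = 0.05 and 2.2 points at R² = 0.15.
- ρ = 0.7: power is about 97.6%. The difference is 0.3 and 0.6 points respectively.

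The interval-width and type I error columns do not depend on ρ.

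**The case against.** The strongest reply is that this is an editorial slip in a condensed article. The labels for random and fixed effects attached to centre and pain score under Phase 2 are modelling terms, which suggests that both were meant to enter the analysis. Sites were added to a trial that began with one, so the two-variable lists may simply not have been updated. That is plausible but cannot be confirmed from the document. It does not remove the point, because the section that defines the primary model gives an explicit and incomplete list.

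A reader might also infer more than the text supports:

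- **That the treatment effect is biased or false positives become likelier.** Neither follows. Omitting balanced strata leaves the estimate unbiased and takes the type I error below 5%.
- **That adjustment would raise power from 80% to between 82% and 86%.** The 80% applies when the two variables explain nothing. If they do explain variance, the model without them also gains from the balanced allocation, so the like-for-like gain is 1.4 to 4 points at R² of 0.05 to 0.15. The document gives no reason to exclude an R² near zero, where there is no gain.
- **That two rival primary models are specified.** Only the Statistical analysis section specifies one; the Phase 2 labels are at most a hint of another.
- **That a random centre effect is an error.** With three sites the between-centre variance rests on 2 degrees of freedom and is poorly estimated, but that variance is not the target. With allocation balanced within centre, the treatment contrast is little affected by the choice.

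**Conclusion.** The point holds as a mismatch between randomisation and primary analysis: four stratification variables in one section, two in the model and in the other description of allocation. The consequence is a loss of efficiency, not a threat to validity. For residual R² between 0 and 0.15, the interval is 0% to 8.5% too wide, the actual type I error 5.0% to 3.4%, and the power shortfall 0 to about 4 points at 154 per arm and SD 12.5. The shortfall is smaller once the baseline adjustment is counted. These figures rest on the assumed R² range, on allocation that balances the arms on centre and pain score, and on a two-sided 5% test. The sample size stands. This should be fixed, but the trial's conclusions do not depend on it.

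**What to change.** Make the three sections (Phase 2 design, Phase 2: RCT of CBTI versus usual care, and Statistical analysis) list the same four stratification variables. Reword the Statistical analysis section so that the primary model contains baseline FES-I, gender, strength-and-balance referral, pain score in the form used at randomisation, and study centre, and apply the same set to the similar secondary-outcome models. State whether centre is fixed or random. With three sites a fixed effect is simpler, but either is acceptable.

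The cost is wording only. Both added variables are already held in the randomisation system. If pain score enters as a single term and centre as a three-level fixed effect, the model gains 1 + 2 = 3 parameters against about 308 patients with outcome data. No new data, visits or recruitment are needed.
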